***How to deal with an AE:***

If an AE occurs, the investigator may:

- Continue the strategy
- Temporally or permanently stop the strategy

In addition, monitoring will be intensified and all measures to prevent the occurrence of an AE will be taken by the investigator with an immediate and explicit notification to the sponsor.

### Conditions and duration of follow-up for an AE

Each adverse event will be followed up until its complete resolution (stabilization to a level considered acceptable by the investigator, or a return to the previous state), even if the patient has left the trial.

### Supervisory board

No supervisory board was considered necessary.

# Statistics

Statistical analysis will be performed by [name], using R v.3.6.0 *(R Foundation for Statistical Computing).*

## Statistical methods

A detailed analysis plan will be developed prior to the start of the study. The plan will be modified, if necessary, before the statistician is unblinded.

Oatient characteristics will be described by randomization group as number and percentages for categorical variables and mean (standard deviation) or median (25th and 75th percentile) for continuous variables, depending on their distribution.

The main analysis will be conducted on an intention-to-treat basis. However, data for patients withdrawing their consent during the study, in accordance with French law, will not be analyzed.

The primary endpoint (percentage of patients requiring intubation or non-invasive ventilation at 2 pressure levels, or who died within 28 days of inclusion) will be compared between the 2 groups (PP and usual care) by a Mantel-Haenszel 2-test stratified on the stratification variables #2 and #3 (SpO2 and BMI). The effect of the intervention will be expressed in terms of absolute risk difference and its 95% confidence interval (CI). The result of this analysis will be confirmed by a mixed-effect logistic regression analysis, with the recruiting center as the random effect and the study intervention and the stratification variables 2 and 3 as fixed effect variables. Interaction terms between the stratification variables and the intervention will be introduced into the model and retained only if they show a significant effect on the frequency of the outcome. Logistic regression analysis will be used to estimate the odds ratio and its 95% CI.

The binary secondary endpoints (intubation rate, rate of non-invasive ventilation at 2 pressure levels, rate of transfer to ICU, mortality) will be compared between the groups using the same method.

The time to clinical improvement (decrease of 2 points on the WHO scale) will be compared between groups by log rank test and presented as Kaplan-Meier curves. The difference in risk between the groups will be expressed as a hazard ratio (HR) and its 95% CI. This analysis will be secondarily adjusted for stratification variables, and possibly other covariables that would be misbalanced between groups, using a Cox proportional model provided the proportional assumption is verified.

The durations (of oxygen therapy, non-invasive ventilation, hospitalization), will be compared between groups by Mann-Whitney U test adjusted for stratification variables [KAWAGUCHI; Statistics in Biopharmaceutical Research; 2011]. The difference in duration (of oxygen therapy, non-invasive ventilation, hospitalization) between groups will be expressed by its median and 95% CI obtained by bootstrapping (2000 unstratified samples).

We will conduct a per-protocol analysis including only patients of the intervention group who laid in a prone position for at least 2 hr each day, and patients of the usual care group who never laid in a prone position.

The above analyses will be repeated in prespecified subgroups formed according to the stratification variables #2 and #3 (SpO2 and BMI).

No interim analysis is planned.

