## Measures to reduce and avoid bias

### Randomization

Randomization will be centralized via a website.

Randomization will be stratified according to the following three parameters:

- **According to the center**
- **Body mass index (BMI) < 30 kg.m^-2^ or not**
- **SpO_2_ (measured by pulse oximetry) < 95% or ≥ 95% on 5-L/min test for 5 min before randomization**

How SpO_2_ will be measured for stratification will be standardized: in patients already included but not yet randomized, SpO_2_ will be systematically measured after 5 min of 5-L/min nasal O_2_ therapy with a moderate concentration mask.

A randomization list will be established beforehand by a clinical study technician, by permuted blocks, whose size will remain unknown to the investigators. The strata are as follows:

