## Emergency treatment

If PP induces a major decrease in SpO2 for more than 5 min or a non-resolving tachycardia despite a return to the classical sitting position or an adaptation of the oxygenation or non-invasive ventilation parameters by the clinician in charge of the patient, we will record this event as a non-serious AE if the supine position improves this parameter. However, if, despite the supine positioning, the patient does not show improvement of respiratory parameters, we will record a serious AE related to the PP.

If the respiratory signs deteriorate significantly, the use of non-invasive ventilation with 2 pressure levels or intubation will be possible if the clinician in charge of the patient considers it necessary. If intubation is considered unreasonable because of the evolution of the disease and vital parameters, although the patient would have initially received treatment in the ICU, appropriate care will be implemented for comfort in accordance with the practices of each department.

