## Number of participants to be included in the research

With a rate of lost to follow-up of < 2%, a population of 268 patients would guarantee a power of at least 80% to demonstrate at the 2-sided alpha risk of 5%, a difference of 10% to 14% between the 2 groups concerning the composite primary endpoint (4% vs 14% or 10% vs 24%). The number of patients to be recruited is fixed at 268.

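### Randomisation is stratified by centre, but the primary Mantel-Haenszel test leaves centre out, which makes it mildly conservative if centres differ beyond SpO2 and BMI

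*Protocol*

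**What the plan says.** Protocol, Randomization: "Randomization will be stratified according to the following three parameters". The first listed is "According to the center"; the others are BMI (cut at 30) and SpO2 on the oxygen test (cut at 95%). Allocation is "by permuted blocks, whose size will remain unknown to the investigators". The section then lists the four BMI by SpO2 combinations as the strata. Read together, this means four strata within each centre.

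Protocol, Statistical methods: the primary endpoint is compared by a Mantel-Haenszel test "stratified on the stratification variables #2 and #3 (SpO2 and BMI". On the effect measure: "The effect of the intervention will be expressed in terms of absolute risk difference and its 95% confidence interval (CI". The strata and variance formula for that interval are not given. The result is then to be confirmed by a mixed-effect logistic regression "with the recruiting center as the random effect", with treatment, SpO2 and BMI as fixed effects, giving an odds ratio. The binary secondary endpoints follow the same method.

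The protocol does not give the number of centres, the block size or the expected spread between centres.

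**The concern.** Balancing the arms within each centre removes between-centre differences from the real sampling error of the treatment comparison. A test that pools over centres still counts those differences in its variance. The standard error is then somewhat too large and the p-value too high.

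The protocol itself makes centre differences plausible. Control care is each department's own usual care (Method), the trial is unblinded, and NIV or intubation "will be possible if the clinician in charge of the patient considers it necessary" (Emergency treatment). Two of the three components of the composite therefore depend on local decisions.

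At stake is some precision in the primary result and in every binary secondary endpoint. The primary test and the model meant to confirm it also use different sets of randomisation factors, so a borderline result could fall on different sides of 0.05 partly for that reason.

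**Working it through.** **1. The plan's own figure.** Inputs from Number of participants: 4% vs 14% or 10% vs 24%, two-sided 5%, 80% power, loss under 2%. With n per arm = [1.96·√(2p̄(1−p̄)) + 0.8416·√(p1(1−p1)+p2(1−p2))]² / (p1−p2)²:
- 4% vs 14%: (1.96·√0.1638 + 0.8416·√0.1588)² / 0.01 = 127.4, so 128 per arm, 256 in all, and 256/0.98 gives 262.
- 10% vs 24%: (1.96·√0.2822 + 0.8416·√0.2724)² / 0.0196 = 111.8, so 112 per arm.

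The stated 268 is confirmed. Power at 134 per arm is 82.0% and 86.7%.

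**2. Size of the effect by formula.** With exact balance within centre, the variance is overstated by the between-centre share s = Var(centre rates) / [p̄(1−p̄)]. The standard error is too large by the factor 1/√(1−s), and the true alpha is 2Φ(−1.96/√(1−s)). Assume 12 equal centres with evenly spaced rates, so Var = range²/12 × 13/11.

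| Centre rates | Var | s | SE factor | True alpha |
|---|---|---|---|---|
| 10–24% | 0.00193 | 0.00193/0.1411 = 1.4% | 1.007 | 4.84% |
| 7–27% | 0.00394 | 0.00394/0.1411 = 2.8% | 1.014 | 4.68% |
| 5–35% | 0.00886 | 0.00886/0.16 = 5.5% | 1.029 | 4.37% |

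**3. Simulation A.** 268 patients, 8 or 14 unequal centres, blocks of 4 within centre by BMI by SpO2, normal centre effects on the logit scale. Centre count, block size, patient mix and SD are assumptions. Power is taken at the protocol's two pairs of rates. The last column compares the planned test with an additive linear model containing centre.

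| Centre SD | Type I error, planned test | Power change with additive centre adjustment (points) |
|---|---|---|
| 0 | about 5% | −0.6 to +0.3 |
| 0.5 | 4.4–4.5% | +0.2 to +0.7 |
| 1.0 | 3.6–3.7% | +1.5 to +2.3 |
| 1.5 | 3.2–3.3% | +2.8 to +4.3 |

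**4. Simulation B.** Different assumptions: 5, 12 or 20 centres, about 35% with BMI ≥30, about 30% in the higher-risk SpO2 group. Type I error of the planned test was 4.4–5.3% at SD 0.5 and 4.1–4.9% at SD 1.0 (Monte Carlo error 0.3–0.4 points). This effect is smaller than in A. The planned test kept at least 84% power throughout.

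**5. What the SDs mean.** At a control rate of 14% the logit is ln(0.14/0.86) = −1.815. SD 0.5 gives a 95% range of centre rates from −1.815 ± 0.98, that is 6% to 30%. SD 1.0 gives −1.815 ± 1.96, that is 2% to 54%. SD 1.5 gives 1% to 75%.

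**6. Which adjustment.** Crossing every centre with the four strata gives 8×4 = 32 to 14×4 = 56 cells, averaging 268/32 = 8.4 down to 268/56 = 4.8 patients. In simulation B (4% vs 14%, SD 0.5) full crossing had 82.5% power against 84.8% for the planned test with 12 centres, and 78.8% against 84.2% with 20. About 10 and 24 patients respectively fell in one-arm strata and dropped out.

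Fixed centre terms in a logistic model also fail. At 4% vs 14% the expected events are 134×0.04 + 134×0.14 = 24. With 14 centres averaging 268/14 ≈ 19 patients and a pooled rate of 9%, a centre has no event with probability 0.91^19 ≈ 0.17, so 14×0.17 ≈ 2.3 such centres are expected even if all are the same size. With unequal centres (8–31 patients) about 3 were found on average, and at least one in 96% or more of simulated trials.

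**The case against.** The case for leaving the plan alone is fair in several respects.

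- **The test is valid.** The error is on the safe side, so nobody should infer that the primary analysis risks a false positive. Nor is the trial underpowered: the planned test stays above 80% in the scenarios run at the protocol's rates.
- **The effect is small for ordinary spread.** SD 1.0 or more implies very wide centre rates, and nothing in the protocol supports such values. A reader might infer that the test is conservative whenever centres differ, or that the omission wastes a material number of patients. The first is too strong: the differences must go beyond SpO2 and BMI, and balance within centre must really be achieved, which incomplete blocks in small cells weaken. The second rests only on SD 1.0 to 1.5.
- **Centre is not ignored.** The confirmatory model carries it, and a low-dimensional test backed by such a model is a defensible pattern.
- **The interval is not fully specified.** That it is too wide follows only if it uses the same two-factor strata.
- **A risk difference and a conditional odds ratio differ in scale anyway,** so some discordance would remain after any fix.

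All of this stands, and it limits the point. It does not remove it. The confirmatory model gives an odds ratio and does nothing for the protocol's stated effect measure. The restriction to two factors is written into the protocol, so it is not a detail left open for the analysis plan.

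**Conclusion.** The point holds as a modest mismatch between design and primary analysis. Centre is a randomisation factor, the primary test omits it, and no centre adjustment is described for the risk difference. If centres differ beyond SpO2 and BMI, the test is mildly conservative: type I error is about 4.5% at SD 0.5 and about 3.6% at SD 1.0 in simulation A, and closer to nominal at SD 1.0 in simulation B. The recoverable power is under 1 point at SD 0.5 and about 1.5 to 2.3 points at SD 1.0.

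These sizes rest on assumed centre counts, block size, patient mix and centre spread, and on blocks being kept within centre. The documents do not support calling the primary result invalid, the sample size inadequate, or the interval certainly too wide.

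**What to change.** In Statistical methods, have the primary p-value, risk difference and 95% CI account for all three randomisation factors. For example: the risk difference will be estimated from a linear (identity-link) model with treatment, SpO2 stratum, BMI stratum and centre as additive terms and robust standard errors; very small centres will be pooled by a rule fixed before unblinding.

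Three limits matter:
- Do not cross every centre with the four SpO2 by BMI strata.
- Do not use logistic regression with fixed centre terms, because centres with no events are likely.
- Keep the two-factor Mantel-Haenszel test as a sensitivity analysis.

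The binary secondary endpoints should follow the same change, since they are tied to the primary method. The cost is an amendment of wording; centre is already recorded and already modelled. If centres do not differ at all, up to about 0.6 points of power are lost.

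### The confirmatory logistic model keeps treatment-by-stratum interactions only if significant, so the data decide whether it yields one overall odds ratio; the adjusted Cox model has a similar data-driven clause

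*Protocol*

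**What the plan says.** All of this stands in protocol section 8.1, Statistical methods.

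- **Primary test.** A Mantel-Haenszel test "stratified on the stratification variables #2 and #3 (SpO2 and BMI"), with the absolute risk difference and its 95% CI. No model selection applies to it.
- **Supporting model.** "The result of this analysis will be confirmed by a mixed-effect logistic regression analysis", with centre as random effect and "the study intervention and the stratification variables 2 and 3 as fixed effect variables".
- **Selection rule.** "Interaction terms between the stratification variables and the intervention will be introduced into the model and retained only if they show a significant effect".
- **Output.** "Logistic regression analysis will be used to estimate the odds ratio and its 95% CI". The text does not say which odds ratio is meant once an interaction has been kept.
- **Reach.** Intubation, non-invasive ventilation, ICU transfer and mortality "will be compared between the groups using the same method".
- **Time to clinical improvement.** The main comparison is a log-rank test. A secondary analysis adjusts for the stratification variables and "possibly other covariables that would be misbalanced between groups, using a Cox proportional model provided the proportional assumption is verified". No variables are listed and imbalance is not defined.
- **Subgroups.** "The above analyses will be repeated in prespecified subgroups formed according to the stratification variables #2 and #3 (SpO2 and BMI").

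**The concern.** A model that confirms a primary result should estimate the same quantity whatever the data show. Here its content depends on significance tests run on the trial's own data. Without interactions, the intervention coefficient is one log odds ratio common to all strata. With an interaction kept, two or more odds ratios exist, and the printed coefficient depends on how the strata are coded. A supporting analysis could then appear to contradict the Mantel-Haenszel result, or appear significant when that result is not, because of coding rather than evidence. The binary secondary endpoints inherit the same ambiguity.

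The Cox clause is a milder case of the same thing. After randomisation, a baseline imbalance is chance and does not show that a covariate is prognostic. The hazard ratio is non-collapsible, so what it estimates depends on which covariates are in the model. In an open-label trial (Blinding methods), that choice is better closed before the data are seen.

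**Working it through.** **1. The plan's own figure.** Section 8.2 gives 268 patients for at least 80% power at two-sided 5%, with under 2% lost, for 4% vs 14% or 10% vs 24%. Per arm, with p̄ the mean of the two rates:

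n = [1.96·√(2p̄(1−p̄)) + 0.8416·√(p₁(1−p₁) + p₂(1−p₂))]² / (p₁−p₂)²

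- 4% vs 14%: [1.96·√0.1638 + 0.8416·√0.1588]² / 0.01 = 127.4, so 128 per arm; 256/0.98 gives 262 in total.
- 10% vs 24%: [1.96·√0.2822 + 0.8416·√0.2724]² / 0.0196 = 111.8, so 112 per arm; 224/0.98 gives 229 in total.
- Power at 134 per arm is 82.0% and 86.7%.

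The stated power is reproduced. It refers to the primary comparison, which the selection rule does not touch.

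**2. How often a term is kept.** There are two candidate interactions (treatment by SpO2, treatment by BMI). The only level given is P<0.05 (section 8.3), and applying it to these tests is an assumption. With no true interaction and independent tests, P(at least one kept) = 1 − 0.95² = 9.75%.

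**3. What the coefficient then means.** Let T be treatment and S the SpO2 stratum, coded 0/1.

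- No interaction: logit p = a + bT + cS + …; exp(b) is the common odds ratio.
- Interaction kept: logit p = a + bT + cS + gTS + …; exp(b) is the odds ratio where S = 0, and exp(b+g) is that where S = 1.
- Interaction kept, S centred at its mean: b is the log odds ratio at the average stratum mix, close to the common one.

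**4. Consequence if b under 0/1 coding is read as the overall effect.** Simulation, 6,000 trials per row, N = 268. Assumptions not in the protocol: 40% with SpO2 <95%, 40% with BMI ≥30, prognostic odds ratios 2.5 and 1.5, no centre effect, no true interaction. Coverage is that of the nominal 95% CI for the common odds ratio.

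| Control vs prone | Term kept | Rejects, fixed model | Rejects, selected model | Rejects when a term is kept | Coverage | SE ratio when kept |
|---|---|---|---|---|---|---|
| 24% vs 24% | 9.9% | 4.9% | 7.3% | 29.1% | 92.6% | 1.42 |
| 14% vs 14% | 9.0% | 5.0% | 7.6% | 33.8% | 92.3% | 1.54 |
| 24% vs 10% | 8.5% | 88.2% | 85.1% | 47.8% | 92.9% | 1.44 |
| 14% vs 4% | 3.1% | 83.0% | 82.0% | 33.0% | 95.5% | 1.50 |

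The excess comes from the trials with a kept term. In the first row they contribute 0.099 × 0.291 = 2.9 points of the 7.3%; in the second, 0.090 × 0.338 = 3.0 points of the 7.6%. When a term is kept, the odds ratio moves by a median factor of 1.9 to 3.4 from the main-effects value.

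**5. Same rule, different coding.** 4,000 trials per scenario, n = 262, with SpO2 <95% in 50% and other assumptions as above.

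| Null rate | Type I, 0/1 | Coverage, 0/1 | Type I, centred | Coverage, centred |
|---|---|---|---|---|
| 14% | 6.9% | 93.1% | 5.0% | 95.0% |
| 24% | 7.9% | 92.1% | 5.1% | 94.9% |

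At 24% vs 10%, power with centred strata is 86.2%, against 86.6% with no interactions. At 14% vs 4%, a term is kept in 3.6% of trials. So the rule keeps terms at the rate in step 2, but the inflation comes from how the coefficient is coded and read.

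**6. Cox clause.** The protocol gives no covariate list and no threshold, so no size can be derived. The point rests on the wording.

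**The case against.** The strongest reply is that the primary analysis is fully fixed and the logistic model only supports it. A reader might infer from step 4 that the trial's type I error is 7–8%. The documents do not support that: the figure belongs to one coefficient in a supporting model.

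A reader might also infer that the confidence interval from this model must undercover. That does not follow either. The protocol prescribes neither 0/1 coding nor reading the reference-stratum coefficient as the overall effect. An analyst who kept an interaction would usually report stratum-specific odds ratios, and the SpO2 and BMI subgroups are already planned. With centred strata the inflation almost vanishes, and at 14% vs 4%, the scenario that drives the sample size, coverage holds even under 0/1 coding.

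On the Cox model, it would be too strong to say that every imbalanced covariate is added. The text makes the addition optional, and the adjusted analysis is secondary to the log-rank test. A separate analysis plan, announced in section 8.1 and not shown here, may name the covariates.

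These replies lower the priority, but the point stands. Retention by significance is a rule the protocol states, not a detail it leaves open, and it conflicts with asking the same model for one confirmatory odds ratio. An analysis plan that followed the protocol would inherit both rules. Optional inclusion of imbalanced covariates adds discretion.

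**Conclusion.** The concern holds at moderate priority and is confined to supporting and secondary analyses. With no true interaction, the rule replaces the single odds ratio in up to about 10% of trials (about 3–4% at 14% vs 4%). Under 0/1 coding the coefficient is then a reference-stratum effect with a standard error about 1.4–1.6 times larger. Only if it is read as the overall effect does its type I error reach about 7–8%, with coverage of about 92–93%; centring leaves almost no inflation. The 9.75% needs only the 5% level, independent tests and Wald tests that hold their level. The other sizes rest on the assumed stratum prevalences, prognostic odds ratios and absence of a centre effect. The Mantel-Haenszel test, the risk difference and the 268 patients are unaffected. The Cox clause is an unjustified data-driven choice of unquantified effect.

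**What to change.** Change the wording of section 8.1, and of the analysis plan if it repeats these rules, before the statistician is unblinded:

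1. Fix the confirmatory logistic model, for the primary and the binary secondary endpoints, as intervention, SpO2 stratum, BMI stratum and random centre, with no interaction terms whatever their p-values.
2. Fit the interactions in a separate model. Report the tests with the stratum-specific effects as part of the planned subgroup analysis.
3. Delete the clause on imbalanced covariables. Adjust the Cox model for the stratification variables and, if wanted, for baseline prognostic covariates named before unblinding and used regardless of imbalance.

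The cost is wording only: no extra patients and no change to the primary analysis. Extra Cox covariates, if any, can be chosen from baseline data already collected.

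### Time to clinical improvement is the one endpoint whose main test ignores the randomisation strata, and its secondary Cox model may add covariates chosen by observed imbalance

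*Protocol*

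**What the plan says.** Protocol section 5.5 (Randomization): "Randomization will be stratified according to the following three parameters", namely centre, BMI (below 30 or not) and SpO2 (below 95% or not on a standard oxygen test).

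Protocol section 8.1 (Statistical methods) then treats the endpoints as follows.

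- Primary endpoint: a Mantel-Haenszel test "stratified on the stratification variables #2 and #3 (SpO2 and BMI"), confirmed by a mixed logistic model with centre as a random effect. The binary secondary endpoints use the same method.
- Durations: "compared between groups by Mann-Whitney U test adjusted for stratification variables".
- Time to improvement: "The time to clinical improvement (decrease of 2 points on the WHO scale) will be compared between groups by log rank test", with Kaplan-Meier curves and a hazard ratio. No stratification is mentioned at this step.
- Adjustment of that last comparison: "This analysis will be secondarily adjusted for stratification variables, and possibly other covariables that would be misbalanced between groups". The method for this step is named with a condition attached: "using a Cox proportional model provided the proportional assumption is verified".

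On changes to the analysis plan, the same section says: "The plan will be modified, if necessary, before the statistician is unblinded".

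**The concern.** There are two separate issues, both confined to the first-listed secondary endpoint.

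**The main test.** Stratified randomisation balances the arms within strata. If the strata predict outcome, a test that ignores them uses a variance that is too large for the design. It rejects less often than its nominal level under no effect and loses power under a real one. The protocol avoids this for its other endpoints and gives no reason for the exception.

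**The covariate rule.** In a randomised trial a baseline difference between arms is chance. Adjustment is worthwhile when a covariate is prognostic, whether or not it happens to differ. The protocol's own scale shows the problem. Section 4.1 admits patients on conventional oxygen (level 4 in Appendix 4) and on high-flow oxygen (level 5). A two-level improvement means reaching level 2, out of hospital, for the first group, and level 3, in hospital without oxygen, for the second. The baseline device therefore shapes the event itself, yet the rule would leave it out if it happened to be balanced. The rule also needs the data split by allocated group, so the final covariate set cannot be settled while the statistician is still fully blind. That fits poorly with the protocol's safeguard on plan changes.

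**Working it through.** **1. The plan's own figure.** No power is stated for time to improvement. The only sample-size claim (section 8.2) is that 268 patients "would guarantee a power of at least 80% to demonstrate at the 2-sided alpha risk of 5"% on the primary endpoint. With pooled variance and no continuity correction,

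n per arm = [1.96·√(2·p̄·q̄) + 0.8416·√(p₁q₁ + p₂q₂)]² / (p₁ − p₂)².

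- 4% vs 14%: (1.96·√0.1638 + 0.8416·√0.1588)² / 0.01 = 127.4, so 128 per arm and 256 in total; 256/0.98 = 262 after 2% loss.
- 10% vs 24%: (1.96·√0.2822 + 0.8416·√0.2724)² / 0.0196 = 111.8, so 112 per arm and 224 in total; 224/0.98 = 229.

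Power at 134 per arm is 82.0% and 86.7%. The stated figure is reproduced, and nothing below alters it.

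**2. The two tests.** The log-rank statistic is Z = Σ(O − E)/√ΣV over event times in the whole sample. The stratified version computes O − E and V inside each of the four BMI-by-SpO2 strata and then sums.

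**3. Inputs to the simulation.** From the protocol: 268 patients, 1:1, blocked within strata, 28 days, two-sided 5%. **Assumed, because the documents give no figures:** 75% improved by day 28 at average covariate values in the control arm, 50% with SpO2 below 95%, 35% with BMI of 30 or more, treatment hazard ratio 1.45, exponential times. There were 1,500 trials per scenario; the simulation standard error is about 0.6 points near 5% and 1.1 points near 78%.

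A closed-form check with no prognostic strata: events = 134·[0.75 + (1 − 0.25^1.45)] = 134·(0.750 + 0.866) ≈ 217. Power = Φ(½·√217·ln 1.45 − 1.96) ≈ Φ(0.78) ≈ 78%. This agrees with the first row below.

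**4. Results.**

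| Prognostic HR, SpO2 / BMI | Power, plain | Power, stratified | Gain (points) | Type I error, plain | Type I error, stratified |
|---|---|---|---|---|---|
| 1.0 / 1.0 | 79.3% | 78.5% | −0.8 | 4.3% | 3.9% |
| 0.7 / 0.85 | 76.5% | 77.9% | 1.4 | 4.9% | 5.3% |
| 0.5 / 0.8 | 72.3% | 77.5% | 5.2 | 3.9% | 5.3% |
| 0.35 / 0.7 | 63.5% | 75.5% | 12.0 | 2.9% | 4.1% |

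The first two gains are within simulation error of zero. A Cox model with SpO2 and BMI fixed in advance gives 79.1%, 78.1%, 78.3% and 75.9%, close to the stratified test. With a treatment hazard ratio of 1.5, a run with 75% improved by day 28 gave gains of about 0, 1.5, 6 and 11 points at SpO2 hazard ratios of 1, 0.6, 0.4 and 0.3. A variant with 40% of patients in each risk category gave about 14 points at the 0.3 extreme.

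**5. The covariate rule.** Add five independent baseline covariates, each prognostic (assumed hazard ratio 0.75 per SD), and call one imbalanced if the arms differ by more than 0.1 SD. With no treatment effect, the adjusted Cox test rejects in:

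- 4.5% to 5.7% of trials if every imbalanced covariate is added mechanically;
- 9.1% to 9.6% if the analyst may report the most favourable of the models that the imbalanced covariates allow.

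These rates concern the adjusted model alone. The log-rank result is the same whatever covariates are chosen.

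**The case against.** **The main analysis is fixed and errs on the safe side.** The protocol names the test, the curves, the effect measure and a secondary Cox adjustment for the stratification variables. A reader might infer that the plan leaves the whole comparison to be chosen after the data are seen, or that the plain log-rank can manufacture a benefit. Neither is supported: the test is prespecified, and its type I error was at or below nominal in every scenario of the table. This stands in full.

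**The power loss is conditional.** The documents do not say how strongly SpO2 or BMI predicts improvement. With weak or no prognosis there is no detectable loss, and the large gaps need hazard ratios of roughly 0.3 to 0.4 for one dichotomised reading. This stands, and it is why the size is given as a range.

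**The smaller unadjusted hazard ratio is not a bias.** Marginal and conditional hazard ratios are different quantities, so a value nearer 1 without stratification is not in itself an error. This also stands.

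**The imbalance rule need not inflate error.** Applied mechanically it stays near 5%, and the protocol does not authorise picking the best model. True, but it gives no threshold and makes even the use of the rule optional. Masked group labels would limit the discretion, but the protocol does not provide for them, and they would not mend a criterion that selects on chance.

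**The analysis plan may list covariates.** It may, and the absence of a list or a threshold here is no finding. But a fixed prognostic list would replace the protocol's criterion rather than fill it in, so the sentence itself should change.

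**Conclusion.** The point holds as a moderate improvement to one secondary endpoint.

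- The main test of time to improvement is inconsistent with the protocol's other endpoints. It is valid, but conservative when the strata are prognostic. Stratifying costs nothing measurable if they are not, and gains about 0 to 12 points of power over assumed SpO2 hazard ratios from 1.0 to about 0.3. The range rests on assumed event rates, prevalences and effects, and the direction does not depend on their exact values.
- The imbalance clause is a poor rule because it ignores prognostic strength and cannot be completed before the groups are compared. Its reach is the adjusted hazard ratio and its interval. The near-doubling of error to 9% to 10% appears only under free selection of the most favourable model, which the text does not license.
- Neither issue affects the primary analysis or the 268 patients.

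**What to change.** In protocol section 8.1, and in the analysis plan to match:

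1. Make the main test of time to clinical improvement a log-rank test stratified on SpO2 and BMI, as for the primary endpoint. Take the hazard ratio and its 95% interval from a Cox model stratified on the same two factors. The plain log-rank can be kept as a sensitivity analysis.
2. State how centre is handled. The present Cox sentence refers to the stratification variables without limiting them to SpO2 and BMI, so centre should not drop out silently. A random or cluster effect would parallel the primary endpoint's mixed model.
3. Replace the imbalance clause with a short list of baseline prognostic covariates, for example age and baseline oxygen device, fixed before the statistician is unblinded.

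The cost is a few sentences. Age and oxygen device at entry should be obtainable from the hospital record, from which section 5.6 already draws all data not listed there. The sample size does not change.
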